## Abstract

**Background:**

Epicardial adipose tissue (EAT) is a newly discovered independent risk factor for coronary atherosclerosis. There is a scarcity of information on the reduction of EAT volume to reduce atherosclerosis risk. Coronary computed tomography angiography (CCTA) has emerged as a noninvasive imaging method for the analysis of coronary atherosclerosis and EAT volume. The purpose of this trial is to determine whether olmesartan medoxomil is effective at both treatment of coronary atherosclerosis progression and EAT volume reduction in patients with coronary atherosclerosis detected by CCTA.

**Methods/design:**

This study is a prospective, single-center, open-label, randomized controlled clinical trial aimed at exploring the efficacy of olmesartan medoxomil on coronary atherosclerosis and EAT. A total of 194 patients with coronary stenosis greater than 30 % and less than 70 % detected by CCTA will be randomly divided into olmesartan medoxomil or conventional antihypertensive medication groups (1:1 ratio). The primary outcome measures include coronary atherosclerosis progression and EAT volume reduction, as detected by CCTA at 12 months. The secondary outcome measures include the levels of blood lipids, glucose, high-sensitivity C-reactive protein, IL-6, monocyte chemotactic protein 1, TNF-α, matrix metalloproteinase 9, NO, endothelin 1, adiponectin, and leptin at baseline and after 6 and 12 months.

**Discussion:**

Treatments aimed at reducing EAT volume can eventually achieve an antiatherosclerotic effect. This is the first trial designed to explore the effect of olmesartan medoxomil on both coronary atherosclerosis progression and EAT volume reduction in patients with coronary atherosclerosis detected by CCTA.

**Trial registration:**

ClinicalTrials.gov: NCT02360956.

## Background

### Epicardial adipose tissue and coronary atherosclerosis

Epicardial adipose tissue (EAT) is directly deposited around the pericardium and coronary artery. By autocrine and paracrine means, EAT can generate various kinds of cytokines, inflammatory mediators and free fatty acids. These biological indicators can affect the state of coronary endothelial function and promote inflammation and oxidative stress, which finally aggravate the progression of coronary atherosclerosis [1–3]. A significant amount of clinical research has been conducted to investigate the link between EAT and coronary atherosclerosis. It was claimed that calcified plaque progression in patients without coronary artery disease and in patients with type 2 diabetes mellitus were associated with a larger EAT volume [4, 5]. Epicardial adipose tissue is also an independent predictor of significant coronary stenosis and is independently associated with high-risk coronary plaque features, such as low CT attenuation plaque, thin-cap fibroatheroma and positive remodeling [6]. Not only is EAT, as a special visceral fat, correlated with the increased development of coronary artery atherosclerosis, but it is also associated with adverse coronary events [7].

### Treatment of epicardial adipose tissue and coronary atherosclerosis

There are ample studies exploring the progression of coronary atherosclerosis following pharmacological manipulation. At the time of writing, the use of statins is recognized as an effective treatment; statins can result in decreases in plaque and necrotic core volume, and can also significantly reduce the progression of low attenuation plaque (<30 Hounsfield units) and non-calcified plaque [8, 9]. Other drugs, such as dipeptidyl-peptidase 4 inhibitors [10], a PPARγ agonist (pioglitazone) [11], atorvastatin plus ezetimibe [12], olmesartan [13], have also been reported to have antiatherosclerotic effects, although the effects have not been verified by large-scale studies. As studies show that EAT volume is associated with plaque progression and cardiovascular adverse events, treatments aimed at reducing EAT volume may finally achieve an antiatherosclerotic, preventive effect. However, at the time of writing, limited studies have aimed at reducing both EAT and plaque volume to achieve an antiatherosclerotic effect. A serial coronary computed tomography angiography (CCTA) study recently indicated that intensive statin therapy can reduce the EAT volume of Europeans, but the study failed to demonstrate a relationship among EAT volume reduction, coronary atherosclerosis progression and clinical prognosis [14]; moreover, intensive statin therapy might not be appropriate for Asians. The epidemiological studies and clinical researches show that Asians may have poorer tolerability and safety to intensive statins than white people, owing to genetic differences (variants in structure or polymorphisms) in pharmacokinetics and pharmacodynamics properties [15–17]. It has been claimed that polymorphic variants in cytochrome P450 (CYP450) families that were associated with statin metabolism might result in varying rates of metabolic clearance. CYP450 2C19 slow metabolizer phenotype was reported to be present in approximately 16 % of Asians compared with only about 3 % of white people [18]. Polymorphic variants in the predominant CYP450 isoform, CYP450 3A4, were reported to be associated with a functional decrease in the enzyme’s activity in dyslipidemic Chinese patients [19]. The HPS2-THRIVE study recently also indicated that, using same-dose statin treatment, an excess of increased alanine aminotransferase was seen mainly among Chinese patients (more than three consecutive values above the upper limit of normal of 0.24 %/year compared with 0.02 %/year in Europe) [20]. Moreover, the morbidity of chronic hepatitis B was high in china with nearly 90 million infections. For these reasons, intensive statin therapy may result in higher hepatotoxicity in Asian populations than in white populations, so low- to moderate- dose statin therapy might be more appropriate for Asian populations [15, 16]. Subjects who undergo weight loss exercise, bariatric surgery, or low-dose aspirin therapy can also reduce EAT volume or inflammation, but the effects are weak and these treatments cannot achieve good results in patients with coronary atherosclerosis progression [21–24]. Our aim is to find a drug that reduces EAT volume while inhibiting the progression of coronary atherosclerosis.

In recent years, studies have confirmed that olmesartan medoxomil can improve endothelial function, resist thrombosis, improve tissue reconstruction, and resist oxidative stress to achieve atherosclerosis resistance [13, 25–28]. The latest research shows that olmesartan medoxomil can better inhibit rat epididymal adipose cell hypertrophy and inflammatory reactions [29]. Therefore, we hypothesized that olmesartan medoxomil may also reduce EAT volume, finally achieving an anti-atherosclerosis effect.

### EAT and coronary atherosclerosis imaging with computed tomography

Compared with such invasive methods as intravascular ultrasound, virtual histology intravascular ultrasound, optical coherence tomography, and fractional flow reserve, CCTA has emerged as a noninvasive imaging method that analyzes both coronary atherosclerosis and EAT volume [14, 30]. To date, ample CCTA studies have explored the progression of coronary atherosclerosis following pharmacological manipulation. Thus, in this study, using CCTA as a noninvasive method to analyze both coronary atherosclerosis progression and EAT volume is of significant clinical value.

#### Aims of the main study

The purpose of this study is to determine whether olmesartan medoxomil is effective on both the treatment of coronary atherosclerosis progression and EAT volume reduction in patients with coronary atherosclerosis detected by CCTA.

#### Aims of the anti-atherosclerosis mechanism study

To explore the relationship between coronary atherosclerosis progression and EAT volume reduction.To explore the effect of olmesartan medoxomil on serum levels of blood lipids, glucose, circulating surrogate markers of atherosclerosis inflammation, including high-sensitivity C-reactive protein, IL-6, monocyte chemotactic protein 1 (MCP-1), TNF-α, and matrix metalloproteinase 9 (MMP-9), circulating surrogate markers of endothelial function, including NO and endothelin 1 (ET-1), and circulating surrogate markers of adipose tissue inflammation and metabolism, including adiponectin and leptin at baseline and after 6 and 12 months.

## Methods/design

### Study design

This study is a prospective, single-center (Chinese PLA General Hospital, Beijing, China), open-label, randomized controlled trial of the efficacy of olmesartan medoxomil on coronary atherosclerosis and EAT. Consecutive patients with coronary stenosis greater than 30 % and less than 70 % detected by CCTA will be randomly assigned to olmesartan medoxomil or conventional antihypertensive medication groups (1:1 ratio). Coronary computed tomography angiography will be conducted at the Department of Cardiology (Chinese PLA General Hospital). Primary outcome measures include coronary atherosclerosis progression and EAT volume reduction, as detected by CCTA, at 12 months. Secondary outcome measures include levels of blood lipids, glucose, high-sensitivity C-reactive protein, IL-6, MCP-1, TNF-α, MMP-9, NO, ET-1, adiponectin, and leptin at baseline and after 6 and 12 months. The study design is summarized in Fig. 1.

**Fig. 1 Fig1:**
[figure not shown]
Study flowchart. CCTA, coronary computed tomography angiography; DBP, diastolic blood pressure; EAT, epicardial adipose tissue; SBP, systolic blood pressure

### Clinical inclusion and exclusion criteria

Clinical inclusion criteria are:Age between 18 and 75 years;Coronary artery stenosis between 30 % and 70 % determined by CCTA in essential hypertension patients;Resting diastolic blood pressure between 90 and 110 mmHg;Type A and B for coronary artery vascular lesions.

Clinical exclusion criteria are:Secondary hypertension;Coronary artery stenosis less than 30 % or greater than 70 %, as determined by CCTA;Severe arrhythmia;Severe cardiac insufficiency or left ventricular dysfunction (left ventricular ejection fraction < 30 %);Severe hepatic or kidney insufficiency;Resting systolic blood pressure > 200 mmHg or resting diastolic blood pressure >110 mmHg;Contraindications to treatment with olmesartan medoxomil (allergy, glaucoma, digestive ulcer, currently taking phosphodiesterase-5 inhibitor);Severe calcification, distortion or type C coronary artery vascular lesions;Pregnancy;Unwillingness or inability to provide informed consent.

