#### Definition of coronary atherosclerosis plaque progression

We will use QAngio CT post-processing software (QAngioCT Research Edition version 2.1.0, Medis Medical Imaging Systems, Leiden, the Netherlands) to evaluate all CCTA data. All three vessels will be assessed in each patient using the 15-segment American Heart Association model for coronary segment classification [32]. Only segments with a diameter ≥2.0 mm and without stent implantation will be considered for analysis. Parameters including minimal lumen diameter, percent diameter stenosis, minimum lumen area, plaque burden, plaque volume, vascular remodeling index, plaque type classification (calcification, necrosis, fiber, and fiber lipid plaques) based on segments will be analyzed using QAngio CT post-processing software.

Coronary atherosclerosis progression is defined as ≥10 % diameter reduction or progression of a pre-existing coronary stenosis or ≥0.2 mm reduction or progression of the minimal luminal diameter in the lesion [30].

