### Study outcomes

The primary outcome measures are coronary atherosclerosis progression and EAT volume changes, as detected by CCTA at 12 months.

The secondary outcome measures includeThe relationship between coronary atherosclerosis and EAT;Serum levels of blood lipids, glucose, circulating surrogate markers of atherosclerotic inflammation including high-sensitivity C-reactive protein, IL-6, MCP-1, TNF-α, and MMP-9, individual circulating surrogate markers of endothelial function including NO and ET-1, and individual circulating surrogate markers of adipose tissue inflammation and metabolism including adiponectin and leptin at baseline and after 6 and 12 months.

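### A patient can enter on a stenosis that the progression endpoint never reads, because the entry rule sets no vessel-size or stent condition and the endpoint does

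*Protocol article*

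**What the plan says.** **Entry.** In the protocol article, Clinical inclusion and exclusion criteria, the lesion requirement is "Coronary artery stenosis between 30 % and 70 % determined by CCTA in essential hypertension patients", together with "Type A and B for coronary artery vascular lesions". The lesion exclusions are stenosis outside that range and "Severe calcification, distortion or type C coronary artery vascular lesions". No minimum vessel diameter is set, and earlier stenting is not an exclusion. The Abstract and Study design repeat the stenosis range, also without a segment condition.

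**Endpoint.** In Definition of coronary atherosclerosis plaque progression, all three vessels are read on a 15-segment model, but "Only segments with a diameter ≥2.0 mm and without stent implantation will be considered for analysis". Progression is a change in diameter or "progression of a pre-existing coronary stenosis", or "≥0.2 mm reduction or progression of the minimal luminal diameter in the lesion".

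**Use.** Under Study outcomes, "The primary outcome measures are coronary atherosclerosis progression and EAT volume changes, as detected by CCTA at 12 months". Statistical analysis makes the patient the unit of analysis. Sample size calculation rests on progression rates of 30 % and 13 %, and its 10 % allowance is for loss to follow-up.

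**The concern.** Entry is decided on any coronary segment; progression is read on a subset of segments. Take a patient whose only 30 to 70 % stenosis is inside a stent or in a vessel under 2.0 mm. That patient meets every listed criterion, yet the lesion that brought them into the trial is not read for this primary outcome. Two things can follow:

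- Another stenosis lies in an analysable segment. The patient is then scored on disease other than the disease that qualified them, and it may be milder.
- No analysable segment holds any stenosis. There is then no pre-existing stenosis or lesion in which change can be scored. The patient either counts as a non-progressor whatever the treatment does, or drops out of the progression analysis.

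The sample size calculation takes every followed patient as scorable at the assumed rates, so any unscorable patients reduce power.

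**Working it through.** **1. The two rules side by side**

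| Feature of the lesion | Entry rule | Progression reading |
|---|---|---|
| Stenosis grade | 30 to 70 % | any pre-existing stenosis or lesion |
| Segment diameter | no condition | at least 2.0 mm |
| Stent | no condition | unstented only |
| Lesion type | A or B; not C, not severely calcified or distorted | no further condition |

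Neither set contains the other. The entry set includes stented and small segments that the endpoint leaves out. The endpoint set includes stenoses below 30 % that do not qualify for entry. A qualifying lesion outside the endpoint set does not by itself make the patient unscorable; that requires no stenosis of any grade in any unstented segment of at least 2.0 mm.

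**2. The protocol's own sample size**

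Inputs, all from Sample size calculation: 30 % versus 13 %, two-sided α = 0.05, β = 0.2, 1:1 allocation. With the unpooled variance:

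n per arm = (1.960 + 0.842)² × (0.30 × 0.70 + 0.13 × 0.87) / 0.17² = 7.849 × 0.3231 / 0.0289 = 87.75

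This gives 88 per arm and 176 in total, as stated. Then 176 × 1.10 = 193.6, so 194, also as stated. The pooled-variance formula gives 91 per arm (182), so the unpooled form is used below.

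**3. Power when a share q is unscorable**

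The documents do not give q; the values below are assumptions. Power = Φ(Δ/SE − 1.960), with Δ = p₁ − p₂ and SE = √{[p₁(1 − p₁) + p₂(1 − p₂)]/n}.

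At q = 0: SE = √(0.3231/88) = 0.0606, Δ/SE = 2.806, power 80.1 %.

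- *Dropped:* rates unchanged, n = 88(1 − q).
- *Counted as non-progressors:* n = 88, both rates multiplied by (1 − q).

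| q (assumed) | n per arm if dropped | Power, dropped | Rates if counted as non-progressors | Power, non-progressors |
|---|---|---|---|---|
| 0 | 88.0 | 80.1 % | 30.0 % v 13.0 % | 80.1 % |
| 2 % | 86.2 | 79.3 % | 29.4 % v 12.7 % | 79.1 % |
| 5 % | 83.6 | 78.1 % | 28.5 % v 12.4 % | 77.4 % |
| 10 % | 79.2 | 75.9 % | 27.0 % v 11.7 % | 74.5 % |

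A test with pooled null variance gives 78.9 % at q = 0 and falls in the same way. The gap between 78.9 % and 80.1 % comes from the formula and not from the segment rule.

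**4. What it would take to make up the loss**

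Keeping 176 scorable patients and the protocol's own factor of 1.10 requires:

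- q = 2 %: 176/0.98, so 180; × 1.10 = 198
- q = 5 %: 176/0.95, so 186; × 1.10 = 204.6, so 205
- q = 10 %: 176/0.90, so 196; × 1.10 = 215.6, so 216

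The plan has 194.

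**5. Patients scored on other lesions**

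No figure can be put on this group. The documents give no progression rate for lesions other than those qualifying for entry.

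**The case against.** The strongest reply is that the endpoint is not tied to the qualifying lesion. It covers all three vessels and has no 30 % floor, so a patient who qualifies on a stented or small segment will often have another stenosis that can be read. This stands. A reader might infer that every such patient is unscorable from randomisation, and the text does not support that.

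Second, the software rule is applied "to evaluate all CCTA data", which on its face includes the baseline scan, so the site may already screen under the same segment rule. It may, but no section says that the entry stenosis is read that way, and the flowchart in Fig. 1 is not available here.

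Third, the stent clause does not prove that stented patients will be enrolled; it could also refer to stents placed during follow-up. That is fair. Still, prior stenting is not excluded at entry, and the small-vessel mismatch does not depend on stents.

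Fourth, handling of non-evaluable patients and analysis sets are commonly left to a full protocol or SAP. Agreed, and their absence is not the point here. The point is that two rules stated in this article differ in scope; an analysis plan cannot change whom the entry rule admits.

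Finally, q is unknown. A reader might infer that the stated 80 % power is simply not delivered. The documents do not support that: by the protocol's own formula the loss is about one percentage point at q = 2 %.

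**Conclusion.** The mismatch is real and its consequences are modest. A patient can qualify on a lesion that the progression endpoint never reads, and is then scored on other disease or, if none is analysable, cannot be scored.

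The unscorable share is undocumented and may be small. On the assumptions above, power for progression goes from about 80 % to about 79 % at q = 2 %, 77 to 78 % at 5 % and roughly 75 to 76 % at 10 % (74.5 % at the lowest). The 10 % allowance is for loss to follow-up and does not cover this.

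The condition is fixed before treatment, so it should fall equally on both arms. The cost is dilution or lost patients, not bias, provided handling is set without regard to arm. The other primary outcome, epicardial fat volume, does not depend on segments. This is a cheap improvement of low priority.

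**What to change.** **Patients still to be enrolled** (recruitment was ongoing according to Trial status): add to the inclusion criteria that at least one 30 to 70 % stenosis must lie in a segment that the progression endpoint will analyse, that is, at least 2.0 mm in diameter and unstented on the baseline CCTA.

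**Patients already randomised:** define the progression analysis set as those with at least one stenosis of any grade in an analysable segment on the baseline CCTA, read without knowledge of arm. The 30 to 70 % range is not needed here because the endpoint definition has no such floor. Since the condition uses only the pre-treatment scan, it does not bias the comparison. Keep all patients in the analysis of epicardial fat volume.

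**Cost:** one line in the eligibility criteria and one line defining the analysis set. No new scan is needed, because segment diameter and stents can be read on the baseline CCTA. The downside is slightly fewer eligible patients.

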### Randomization

Information regarding the study will be provided to the patient at the Department of Cardiology. Once informed consent is obtained, the patient will be randomized at the Department of Cardiology. Subjects will be randomized to either olmesartan medoxomil or conventional antihypertensive medication groups (1:1 ratio). Participants will be randomized before the first treatment using a blocked randomization procedure (computerized random numbers) and will incorporate minimization to ensure matching for age, sex, body mass index, and hypertension grade.

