#### CCTA image post-processing

All CCTA data will be sent to the Syngo Multi-Modality Workplace for post-processing. Two independent experienced observers who are unaware of the patients’ clinical information will evaluate the CCTA data in different modes, including maximum intensity projection, volume rendering, curved-planar reconstructions, and the original transaxial images. Disagreements in data analysis between the two readers will be resolved by consensus reading.

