### Sample size calculation

This trial is an open-label randomized clinical trial, so patients will randomly be assigned to olmesartan medoxomil or conventional antihypertensive medication groups (1:1 ratio). The purpose of this study is to verify that olmesartan medoxomil is effective in the treatment of coronary atherosclerosis progression and EAT volume reduction in patients with coronary atherosclerosis detected by CCTA. We also want to elucidate the relationship between coronary atherosclerosis and EAT. The mechanism by which olmesartan medoxomil inhibits coronary atherosclerosis progression will be studied by detecting the serum levels of blood lipids, glucose, circulating surrogate markers of atherosclerosis inflammation including high-sensitivity C-reactive protein, IL-6, MCP-1, TNF-α, and MMP-9, circulating surrogate markers of endothelial function, including NO and ET-1, and circulating surrogate markers of adipose tissue inflammation and metabolism, including adiponectin and leptin.

Studies on coronary atherosclerosis progression rate have had differing results. The combined results of multiple studies indicate that the conventional mean coronary atherosclerosis progression rate is about 30 % [33–35]. We hypothesize that additional olmesartan medoxomil use will reduce the coronary atherosclerosis progression rate to 13 % [36–40]. Using double-side inspection, α = 0.05, β = 0.2, we calculate a total sample size of 176 cases; considering the expected loss to follow-up to be 10 %, the number of cases to be included should be at least 176 × (1 + 10 %) = 194. Therefore, we aim for 97 cases of each group.

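### Blocking and minimization are both named with no rule joining them, and the planned two-group tests ignore the four factors that allocation is meant to balance

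*Protocol article*

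**What the plan says.** Under Randomization, the protocol article describes allocation in one sentence as "using a blocked randomization procedure (computerized random numbers) and will incorporate minimization to ensure matching for age, sex, body mass index, and hypertension grade". It puts the act in time and place: "Once informed consent is obtained, the patient will be randomized at the Department of Cardiology". The Study design section adds the setting: "This study is a prospective, single-center (Chinese PLA General Hospital, Beijing, China), open-label, randomized controlled trial". Image reading is masked: "Two independent experienced observers who are unaware of the patients’ clinical information will evaluate the CCTA data".

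The Statistical analysis section compares groups with chi-square and two-sample t tests. It also plans a multiple logistic regression of progression on treatment group, EAT volume and clinical variables, but it does not list those variables. No adjusted model is given for EAT volume change, the other primary outcome. The Trial status section says that recruitment began in December 2014 and is ongoing.

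**The concern.** There are two linked problems.

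**Allocation.** A permuted-block list fixes the order of arms without reference to who enrols. Minimization works out each assignment from the new patient's factor levels and the allocations so far. A reader cannot tell from the article which of them decides a given patient's arm. The article does not omit the mechanism. It names two and gives no rule between them.

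**Analysis.** Balancing on prognostic factors removes part of the chance variation in the treatment difference. A chi-square or t test that ignores those factors still counts that part in its standard error. The test is then conservative, and the precision that the balancing was meant to buy is not used. How far this applies depends on which mechanism was used, so the unclear sentence on allocation also affects how the planned tests behave.

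**Working it through.** **The plan's own figure.** The documents give no figure for allocation. The sample size is checked only because 194 and 176 are used below. The unpooled two-proportion formula gives n per arm = [0.30 × 0.70 + 0.13 × 0.87] × (1.960 + 0.842)² / 0.17² = 87.75, so 88 per arm and 176 in total. Then 176 × 1.10 = 193.6, or 194. The stated figures are reproduced, and nothing below changes them.

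**How often the two mechanisms disagree.** This was simulated with 194 patients, block lists of size 4 or 6, and range-method minimization on four factors with assumed numbers of levels 2, 2, 3 and 2. Minimization preferred an arm for about 72% of patients. The block list pointed to the other arm for about 33% of all patients. If both rules were applied to everyone, one would have to give way for roughly a third of enrolments.

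**What ignoring the factors costs, for EAT volume change.** Let R² be the share of outcome variance that the four factors explain. The documents give no value, so 0.1 to 0.3 is assumed. With near-perfect balance, the true variance of the treatment difference is (1 − R²) times what the t test assumes. Hence:

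- standard error overstated by the factor 1/√(1 − R²)
- true two-sided level = 2 × [1 − Φ(1.96/√(1 − R²))]

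| Assumed R² | SE overstated by | True level of a 5% test (formula) | Simulated, minimization with no random element | Simulated, preferred arm with probability 0.8 | Simulated, plain blocks of 4 |
|---|---|---|---|---|---|
| 0.1 | 5% | 3.9% | 4.0% | 4.3% | 4.8% |
| 0.2 | 12% | 2.8% | 3.2% | 3.3% | 4.7% |
| 0.3 | 20% | 1.9% | 2.2% | 2.3% | 5.1% |

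The simulations used 4,000 trials of 194 patients each, with the factor levels above and a Monte Carlo standard error of about 0.3 percentage points. A linear model adjusted for the four factors stayed at 4.7% to 5.1% under all three mechanisms. The unadjusted test therefore keeps its level under plain blocks and falls below it under minimization, while the adjusted model is right under either.

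**How predictable allocation could be.** For fixed blocks of size 2m whose size is known to the recruiter, the expected share of assignments certain in advance is 1/(m + 1). That is 50%, 33% or 25% for blocks of 2, 4 or 6, or about 97, 65 or 49 of 194. Best-guess success is 75%, 71% and 68%. For minimization with full knowledge of factors and running totals, best-guess success is 91% with no random element and 75% when the preferred arm has probability 0.8. Someone who knows only the arm totals would guess 71% and 63%. Chance is 50%. Every block size, level and probability here is an assumption.

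**The case against.** The strongest reply is that this is a condensed article. Block size, random element, factor cut-points, concealment and the choice of covariates may all stand in a full protocol or analysis plan that is not shown. That holds, and none of those omissions is counted here. Three stronger readings are tempting, and the documents do not support them.

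- **That the procedure cannot be carried out.** Workable hybrids exist, such as a block list for the first patients or for ties. The sentence might also loosely mean blocks stratified on the four factors. The 33% conflict rate arises only if both rules are applied to every patient, which the article does not say. The text is ambiguous, not impossible.
- **That recruiters can foresee the next arm.** The article does not say that blocks are fixed or that minimization lacks a random element. It gives the department as the place of randomization but does not say who generates or holds the sequence. Selection bias is a conditional risk in a single-centre, open-label trial, not a demonstrated one. Masked image reading limits detection bias and has no bearing on this risk in either direction.
- **That blocking must be dropped.** Minimization at probability 0.8 is guessed correctly 75% of the time with full knowledge, against 71% and 68% for known fixed blocks of 4 and 6. It removes certainty but does not lower guessability on this measure. Choosing between the mechanisms is largely a preference.

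A further reply is that a logistic regression is already planned. It covers only one of the two primary outcomes and does not commit to the four factors. It also includes EAT volume, whose change is itself a primary outcome, so it reads more as a model of association than as the primary treatment comparison.

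**Conclusion.** The point stands as a should-fix on two grounds. First, the article names two allocation mechanisms and no rule joining them. Second, its two-group tests ignore the factors that allocation is said to balance.

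The size of the second depends on how strongly the four factors predict outcome. For EAT volume change, an R² of 0.1 to 0.3 means a standard error overstated by about 5% to 20% and a true level of about 4% down to 2%. If allocation was in fact by plain unstratified blocks, the unadjusted level is correct, and adjustment still gains precision when the factors are prognostic. For progression the direction is the same but the size was not computed. There the gain from adjustment is in the power of the test, and the adjusted odds ratio is conditional on the factors.

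The predictability percentages are scenarios, not facts about this trial.

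**What to change.** 1. **Randomization section.** State the one mechanism used, or the rule that joins the two (for example, which rule decides and when the other applies). State that it has a random element, so that the next assignment is never certain to those who recruit: varied block sizes if blocks are kept, or a probability below 1 for the preferred arm if minimization is kept. Because recruitment is under way, record which procedure was applied to patients already enrolled.
2. **Statistical analysis section.** Make the primary comparison of progression a logistic regression on treatment group, and that of EAT volume change a linear model on treatment group, each adjusted for sex, age, BMI and grade of hypertension. Keep the model that contains EAT volume separate, for the question of how EAT relates to progression.

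**Cost.** This means protocol wording, perhaps a small change to the allocation program, and slightly more analysis work. The four factors are already needed for allocation, and the sample size is unchanged. One practical limit applies. At the planned rates, 176 evaluable patients give about 88 × 0.30 + 88 × 0.13 = 37.8 progression events. The logistic model should therefore be kept lean. With one term per factor plus treatment it has five terms, or about 7.6 events per term.
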